### Current Protocol

The current study protocol at the time of writing is version 5, dated 07/05/2020. Future amendments to the protocol will be reviewed for their impact on this SAP, which will be updated only if necessary. If no changes are required to this SAP following future amendments to the study protocol, this will be documented as part of the Robertson Centre Impact Assessment process.

### Deviations from Those Specified in Study Protocol

No planned deviations from analyses planned in the study protocol.

### Additional Analyses to Those Specified in Study Protocol

No planned additional analyses to those planned in the study protocol.

### Software

Data will be analysed using R version 3.6.2 or SAS version 9.4 or higher versions of those programs.

# Analysis populations

## Efficacy

The intention-to-treat (ITT) population will consist of all participants who consented and provided any baseline data.

The per-protocol (PP) population will consist of all participants who consented and provided any baseline data and attended at least seven out of 14 sessions for IY or two out of six sessions for PInC.

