### Per protocol analysis

The analysis of the primary outcome will be repeated using treatment received instead of allocated treatment in the PP population.

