| Change from baseline | Mean (SD)  Median (IQR)  [Range] | xx.x (xx.x)  xx.x (xx.x, xx.x)  [xx.x, xx.x] | xx.x (xx.x)  xx.x (xx.x, xx.x)  [xx.x, xx.x] | xx.x (xx.x)  xx.x (xx.x, xx.x)  [xx.x, xx.x] |
| Linear regression analysis predicting change from baseline from randomised intervention group adjusting for baseline PSOC, child age and gender | | | | |
|  |  | Adjusted mean difference (95% confidence interval) | | p-value |
| IY vs. PInC | | x.xx (x.xx, x.xx) | | x.xxxx |
| Residual standard deviation | | x.xx | |  |

Table 3.2 Primary outcome - PSOC. ITT population with 12-month follow-up.

|  |  |  | Randomised intervention | |
| --- | --- | --- | --- | --- |
|  |  | All | PInC | IY |
| Baseline | N_OBS_ (N_MISS_)  Mean (SD)  Median (IQR)  [Range] | nn (nn)  xx.x (xx.x)  xx.x (xx.x, xx.x)  [xx.x, xx.x] | nn (nn)  xx.x (xx.x)  xx.x (xx.x, xx.x)  [xx.x, xx.x] | nn (nn)  xx.x (xx.x)  xx.x (xx.x, xx.x)  [xx.x, xx.x] |
| Follow-up | N_OBS_ (N_MISS_)  Mean (SD)  Median (IQR)  [Range] | nn (nn)  xx.x (xx.x)  xx.x (xx.x, xx.x)  [xx.x, xx.x] | nn (nn)  xx.x (xx.x)  xx.x (xx.x, xx.x)  [xx.x, xx.x] | nn (nn)  xx.x (xx.x)  xx.x (xx.x, xx.x)  [xx.x, xx.x] |
| Participants with baseline and follow-up data only | | | | |
| N |  | nn | nn | nn |
| Baseline | Mean (SD)  Median (IQR)  [Range] | xx.x (xx.x)  xx.x (xx.x, xx.x)  [xx.x, xx.x] | xx.x (xx.x)  xx.x (xx.x, xx.x)  [xx.x, xx.x] | xx.x (xx.x)  xx.x (xx.x, xx.x)  [xx.x, xx.x] |
| Follow-up | Mean (SD)  Median (IQR)  [Range] | xx.x (xx.x)  xx.x (xx.x, xx.x)  [xx.x, xx.x] | xx.x (xx.x)  xx.x (xx.x, xx.x)  [xx.x, xx.x] | xx.x (xx.x)  xx.x (xx.x, xx.x)  [xx.x, xx.x] |
| Change from baseline | Mean (SD)  Median (IQR)  [Range] | xx.x (xx.x)  xx.x (xx.x, xx.x)  [xx.x, xx.x] | xx.x (xx.x)  xx.x (xx.x, xx.x)  [xx.x, xx.x] | xx.x (xx.x)  xx.x (xx.x, xx.x)  [xx.x, xx.x] |
| Linear regression analysis predicting change from baseline from randomised intervention group adjusting for baseline PSOC, child age and gender | | | | |
|  |  | Adjusted mean difference (95% confidence interval) | | p-value |
| IY vs. PInC | | x.xx (x.xx, x.xx) | | x.xxxx |
| Residual standard deviation | | x.xx | |  |

Table 3.3 Primary outcome - PSOC. PP population.

|  |  |  | Intervention received | |
| --- | --- | --- | --- | --- |
|  |  | All | PInC | IY |

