| Baseline | N_OBS_ (N_MISS_)  Mean (SD)  Median (IQR)  [Range] | nn (nn)  xx.x (xx.x)  xx.x (xx.x, xx.x)  [xx.x, xx.x] | nn (nn)  xx.x (xx.x)  xx.x (xx.x, xx.x)  [xx.x, xx.x] | nn (nn)  xx.x (xx.x)  xx.x (xx.x, xx.x)  [xx.x, xx.x] |
| Follow-up | N_OBS_ (N_MISS_)  Mean (SD)  Median (IQR)  [Range] | nn (nn)  xx.x (xx.x)  xx.x (xx.x, xx.x)  [xx.x, xx.x] | nn (nn)  xx.x (xx.x)  xx.x (xx.x, xx.x)  [xx.x, xx.x] | nn (nn)  xx.x (xx.x)  xx.x (xx.x, xx.x)  [xx.x, xx.x] |
| Participants with baseline and follow-up data only | | | | |
| N |  | nn | nn | nn |
| Baseline | Mean (SD)  Median (IQR)  [Range] | xx.x (xx.x)  xx.x (xx.x, xx.x)  [xx.x, xx.x] | xx.x (xx.x)  xx.x (xx.x, xx.x)  [xx.x, xx.x] | xx.x (xx.x)  xx.x (xx.x, xx.x)  [xx.x, xx.x] |
| Follow-up | Mean (SD)  Median (IQR)  [Range] | xx.x (xx.x)  xx.x (xx.x, xx.x)  [xx.x, xx.x] | xx.x (xx.x)  xx.x (xx.x, xx.x)  [xx.x, xx.x] | xx.x (xx.x)  xx.x (xx.x, xx.x)  [xx.x, xx.x] |
| Change from baseline | Mean (SD)  Median (IQR)  [Range] | xx.x (xx.x)  xx.x (xx.x, xx.x)  [xx.x, xx.x] | xx.x (xx.x)  xx.x (xx.x, xx.x)  [xx.x, xx.x] | xx.x (xx.x)  xx.x (xx.x, xx.x)  [xx.x, xx.x] |
| Linear regression analysis predicting change from baseline from randomised intervention group adjusting for baseline PSOC, child age and gender | | | | |
|  |  | Adjusted mean difference (95% confidence interval) | | p-value |
| IY vs. PInC | | x.xx (x.xx, x.xx) | | x.xxxx |
| Residual standard deviation | | x.xx | |  |

Table 4.1.1 Secondary outcome – ECBI problem score. ITT population.

|  |  |  | Intervention received | |
| --- | --- | --- | --- | --- |
|  |  | All | PInC | IY |
| Baseline | N_OBS_ (N_MISS_)  N (%) ≤ 11  N (%) > 11 | nn (nn)  nn (xx.x)  nn (xx.x) | nn (nn)  nn (xx.x)  nn (xx.x) | nn (nn)  nn (xx.x)  nn (xx.x) |
| Follow-up | N_OBS_ (N_MISS_)  N (%) ≤ 11  N (%) > 11 | nn (nn)  nn (xx.x)  nn (xx.x) | nn (nn)  nn (xx.x)  nn (xx.x) | nn (nn)  nn (xx.x)  nn (xx.x) |
| Participants with baseline and follow-up data only | | | | |
| N |  | nn | nn | nn |
| Baseline | N_OBS_ (N_MISS_)  N (%) ≤ 11  N (%) > 11 | nn (nn)  nn (xx.x)  nn (xx.x) | nn (nn)  nn (xx.x)  nn (xx.x) | nn (nn)  nn (xx.x)  nn (xx.x) |
| Follow-up | N_OBS_ (N_MISS_)  N (%) ≤ 11  N (%) > 11 | nn (nn)  nn (xx.x)  nn (xx.x) | nn (nn)  nn (xx.x)  nn (xx.x) | nn (nn)  nn (xx.x)  nn (xx.x) |
| Logistic regression analysis predicting change from baseline from randomised intervention group adjusting for baseline ECBI problem score > 11, child age and gender | | | | |

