| Proportion of sessions attended (%) | N_OBS_ (N_MISS_)  Mean (SD)  Median (IQR)  [Range] | nn (nn)  xx.x (xx.x)  xx.x (xx.x, xx.x)  [xx.x, xx.x] | nn (nn)  xx.x (xx.x)  xx.x (xx.x, xx.x)  [xx.x, xx.x] | nn (nn)  xx.x (xx.x)  xx.x (xx.x, xx.x)  [xx.x, xx.x] |

Table 5.2 Attendance at group sessions by sessions – PinC

| Session | Number not withdrawn | Number attended | Percentage attended |
| --- | --- | --- | --- |
| Week 1 | nn | nn | xx.x |
| Week 2 | nn | nn | xx.x |
| Week 3 | nn | nn | xx.x |
| Week 4 | nn | nn | xx.x |
| Week 5 | nn | nn | xx.x |
| Follow-up | nn | nn | xx.x |
| Attended at least 2 sessions | nn | nn | xx.x |

Table 5.3 Attendance at group sessions by sessions – IY

| Session | Number not withdrawn | Number attended | Percentage attended |
| --- | --- | --- | --- |
| Week 1 | nn | nn | xx.x |
| Week 2 | nn | nn | xx.x |
| Week 3 | nn | Nn | xx.x |
| Week 4 | nn | Nn | xx.x |
| Week 5 | nn | Nn | xx.x |
| … | … | … | … |
| Week 14 | nn | Nn | xx.x |
| Attended at least 7 sessions | nn | Nn | xx.x |

Table 6.1 Withdrawals from the intervention

|  |  |  | Randomised intervention | |
| --- | --- | --- | --- | --- |
|  |  | All | PInC | IY |
| Withdrawals | N_OBS_ (N_MISS_)  N(%) No  N(%) Yes | nn (nn)  nn (xx.x)  nn (xx.x) | nn (nn)  nn (xx.x)  nn (xx.x) | nn (nn)  nn (xx.x)  nn (xx.x) |
| Withdrawal reasons | N_OBS_ (N_MISS_)  N(%) Wished to attend another intervention  N(%) Didn’t want to continue  N(%) Couldn’t attend due to ill health  N(%) time commitment  N(%) No reason given | nn (nn)  nn (xx.x)  nn (xx.x) | nn (nn)  nn (xx.x)  nn (xx.x) | nn (nn)  nn (xx.x)  nn (xx.x) |

Table 6.2 Withdrawals from the study

|  |  |  | Randomised intervention | |
| --- | --- | --- | --- | --- |
|  |  | All | PInC | IY |
| Withdrawals | N_OBS_ (N_MISS_)  N(%) No  N(%) Yes | nn (nn)  nn (xx.x)  nn (xx.x) | nn (nn)  nn (xx.x)  nn (xx.x) | nn (nn)  nn (xx.x)  nn (xx.x) |
| Withdrawal reasons | N_OBS_ (N_MISS_)  N(%) Unhappy with baseline questionnaire  N(%) Too busy  N(%) Did not attend baseline assessment… | nn (nn)  nn (xx.x)  nn (xx.x)  nn (xx.x) | nn (nn)  nn (xx.x)  nn (xx.x)  nn (xx.x) | nn (nn)  nn (xx.x)  nn (xx.x)  nn (xx.x) |

Table 7 Summary of adverse events

|  |  |  | Randomised intervention | |
| --- | --- | --- | --- | --- |
|  |  | All | PInC | IY |
| Participants experiencing at least one SAE | N(%) | nn (xx.x) | nn (xx.x) | nn (xx.x) |
| Number of events | N | nn | nn | nn |

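### The per-protocol analysis of PSOC is an as-treated comparison in all but name, its table contradicts its text, and its unequal attendance cuts are unexplained

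*Supplement*

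**What the plan says.** Three places in the SAP define this analysis.

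- **Section 2.1 (Efficacy populations).** The PP population needs consent, any baseline data, and attendance: "attended at least seven out of 14 sessions for IY or two out of six sessions for PInC". It does not say that the sessions must be those of the programme to which the family was randomised. The attendance rows of Tables 5.2 and 5.3 repeat both cuts ("Attended at least 2 sessions" for PInC, "Attended at least 7 sessions" for IY), so the figures are deliberate.
- **Section 3.4.6 (Per protocol analysis).** The primary-outcome analysis is repeated "using treatment received instead of allocated treatment in the PP population".
- **Table 3.3 (PSOC, PP population).** The columns are headed "Intervention received", but the model row reads: "Linear regression analysis predicting change from baseline from randomised intervention group adjusting for baseline PSOC, child age and gender".

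For contrast, the main efficacy set carries no attendance condition: "The intention-to-treat (ITT) population will consist of all participants who consented and provided any baseline data". Section 3.4.1 analyses PSOC by randomised group.

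**The concern.** There are two separate problems.

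**Label and specification.** A per-protocol set normally holds participants who took what they were allocated, compared by allocated arm. Here a family randomised to PInC that attended seven IY sessions meets section 2.1 and is counted as IY under section 3.4.6. Choice of programme then decides group membership, and the reasons for choosing can confound the comparison. Table 3.3 does not settle which variable enters the model, because its header and its model row name different ones.

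**Unequal selection.** A family must attend half of IY to stay in, but only a third of PInC. If more engaged families tend to improve more, the two retained groups can differ with no true difference between the programmes.

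The Study Background asks whether PInC is at least as effective as IY. A full trial with that question would probably give weight to a PP analysis, so the definition should be sound before it is carried forward.

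**Working it through.** **1. The contradiction (no assumptions needed).** Take a family randomised to PInC that attends seven IY sessions and no PInC sessions.

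| Place | How the family is handled |
|---|---|
| Section 2.1 | In the PP set (seven IY sessions) |
| Section 3.4.6 | Counted as IY |
| Table 3.3, columns | Counted as IY |
| Table 3.3, model row | Counted as PInC |

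With no switchers all four agree. With one switcher, the descriptive columns and the regression in the same table describe different groups.

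**2. The plan's own number.** The Sample Size section assumes 100 approached, 60% response and two-thirds retention: 100 × 0.60 × 2/3 ÷ 2 = 20 per arm. This reproduces.

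**3. The cuts.** IY 7/14 = 50.0%; PInC 2/6 = 33.3%.

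**4. Share entering the PP set if every family attends each session with the same probability p in both arms (assumed; binomial tail).**

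| p | IY, at least 7 of 14 | PInC, at least 2 of 6 |
|---|---|---|
| 0.4 | 30.8% | 76.7% |
| 0.5 | 60.5% | 89.1% |
| 0.6 | 85.0% | 95.9% |
| 0.8 | 99.8% | 99.8% |

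The gap closes when attendance is high.

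**5. Selection when engagement varies between families.** Assume each family's attendance probability is uniform on 0 to 1 (mean 0.5, SD 1/√12 = 0.289) in both arms. The number of sessions attended, x out of n, is then equally likely to take any value from 0 to n, and the mean engagement given x is (x + 1)/(n + 2).

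- IY, 7 of 14: retained 8/15 = 53%; mean engagement (10.5 + 1)/16 = 0.719, which is 0.758 SD above average.
- PInC, 2 of 6: retained 5/7 = 71%; mean (4 + 1)/8 = 0.625, which is 0.433 SD above average.
- PInC, 3 of 6: retained 4/7 = 57%; mean (4.5 + 1)/8 = 0.688, which is 0.650 SD above average.

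The spurious difference (IY minus PInC) is the engagement-outcome correlation times the gap. At an assumed correlation of 0.3, the stated cuts give 0.3 × (0.758 − 0.433) = 0.10 SD. A common half-of-sessions cut gives 0.3 × (0.758 − 0.650) = 0.03 SD.

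**6. Range.** A simulation with no true effect used five assumed Beta distributions of engagement (mean attendance 50% to 67%, the uniform among them) and correlations of 0.2, 0.3 and 0.5. It relates the outcome to a normal score of engagement, so its values are a little lower than in step 5 (0.086 rather than 0.10 SD for the uniform case at 0.3).

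| Cuts | Spurious difference, all scenarios | Uniform engagement only |
|---|---|---|
| As stated | 0.04 to 0.17 SD | 0.06 to 0.15 SD |
| Common half | 0.01 to 0.06 SD | 0.02 to 0.05 SD |

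**7. Against sampling error.** For mean attendance of 60%, the simulation retains 67% of IY and 83% of PInC. Applied to 20 per arm, that is about 13 and 17 families. The unadjusted standard error is √(1/13 + 1/17) = 0.37 SD. With the uniform shares (about 11 and 14) it is √(1/11 + 1/14) = 0.40 SD. So 0.10 SD is about a quarter of one standard error (0.10/0.37 = 0.27), and 0.17 SD is under half of one (0.17/0.37 = 0.46).

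**The case against.** **The consequence is small.** The three research questions concern willingness to be randomised, recruitment and retention, and acceptability. None is about efficacy. PSOC is only a proposed primary outcome, its main analysis is intention-to-treat by randomised group, and the PP analysis repeats that one outcome. No stated decision rests on it. This stands and limits the weight of the point.

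**The Table 3.3 model row looks like carry-over.** Tables 3.1, 3.2 and 3.3 share the same row, and Table 4.1.1, an intention-to-treat table, has the reverse slip in its header. Section 3.4.6 states its intention plainly. That probably explains the mismatch but does not remove it, and it leaves the as-treated labelling untouched. No switching rate is given. Table 6.1 lists a wish to attend a different intervention as a withdrawal reason, but does not say that this means the other trial arm.

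**Different cuts may be justified.** A minimum exposure can be specific to a programme, and a 14-session and a six-session programme need not share a percentage. The protocol is not shown and may give the reason. This stands: the fair criticism is that the SAP gives no rationale. A reader might infer that the thresholds are wrong and must be equal fractions, but the documents do not support that.

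**The bias is not established.** A reader might also infer that the comparison is biased towards IY by about 0.10 SD. The documents give neither an attendance distribution nor a link between attendance and outcome. That figure, and its direction, depend on assuming equal engagement in two programmes of very different length. Adjustment for baseline PSOC, child age and gender may absorb part of any bias.

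**Conclusion.** The specification fault is certain. The SAP calls an as-treated comparison per-protocol and names two different grouping variables for the same model. Whether this changes an estimate depends on whether any family switches.

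The unequal cuts make the comparison open to selection bias; they do not show that it is biased. Under equal engagement in both arms, mean attendance of 50% to 67% and correlations of 0.2 to 0.5, all assumed, the spurious difference is about 0.04 to 0.17 SD. It is near zero if attendance is high in both arms and zero if attendance is unrelated to outcome. Within the range shown it stays below the sampling error of about 0.37 SD.

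The feasibility outcomes and the intention-to-treat result are not affected. The correction is worth making because it is cheap and the definition may be carried into a full trial.

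**What to change.** 1. In section 2.1, define the PP population as families who met the stated minimum of the programme to which they were allocated.
2. In section 3.4.6, analyse that population by allocated arm, and make the Table 3.3 header and model row say the same. Correct the Table 4.1.1 header at the same time.
3. If an as-treated analysis is also wanted, give it that name and its own table, and list the switchers.
4. State the reason for the two attendance cuts or cite where it is given. Table 5.2 counts a follow-up session among the six for PInC, so say whether it counts towards the two.
5. Report the number excluded per arm and label the result exploratory. Analysis by allocated arm removes confounding by choice of programme, but it still conditions on attendance after randomisation.
6. Optionally, show a common-fraction cut as a sensitivity analysis. It reduces the selection without removing it (0.10 to 0.03 SD in step 5). A half cut would shrink the PInC PP set from about 71% to 57% under the uniform assumption, or from about 14 to 11 of 20 families. A one-third cut is not a whole number of IY sessions (14/3 = 4.67), so the rounding would need to be stated.

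The cost is SAP wording, two table templates and a rerun on attendance data that the trial already plans to tabulate.

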## Safety

The safety population will consist of all participants who consented.

# Analysis

## Subject disposition

The number of participants in the ITT population and the number of participants in the safety population will be tabulated.

## Baseline characteristics

The following baseline characteristics relating to the child will be summarised in the ITT population:

- Age
- Gender
- Time since diagnosis
- Relationship with main carer
- Being on ADHD medication
- Time since starting ADHD medication (earliest recorded if more than one)
- Other neurodevelopmental diagnosis

The following baseline characteristics relating to the parent will be summarised in the ITT population:

- Age
- Gender
- SIMD
- Relationship with child
- Ethnicity
- Education
- Average household income

## Feasibility outcomes

The following proportions will be calculated:

- the proportion of eligible subjects that was approached;
- the proportion of approached subjects who consented to take part in the trial;
- the proportion of approached subjects who consented to take part in the trial and provide any baseline data;
- the proportion of consented participants who provide any follow-up data;
- the proportion of consented participants in wave 1, 2 and 3 who provide any follow-up data at 12 months;
- the proportion of consented participants in wave 4 who provide any follow-up data at 6 months;
- the proportion of consented participants who provide outcome data for each of the efficacy outcomes separately, overall and by waves 1-3 vs. wave 4.

## Efficacy Outcomes

### Putative Primary Outcome

Change from baseline in PSOC will be analysed in a linear regression analysis predicting change from baseline from randomised intervention group adjusting for baseline PSOC, child age and gender.

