## Study Design

A randomised controlled feasibility trial. The intervention will be delivered in four waves. Participants of waves 1, 2 and 3 will have follow up assessments after 12 months, participants of wave 4 will have follow-up assessments after 6 months.

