## Randomisation

Families will be randomised 1:1 to receive either PInC or IY. No stratification or minimisation is applied.

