### General Principles

Rates will be calculated with Clopper-Pearson^1^ 95% confidence intervals.

Proposed primary and secondary outcome measures will be summarised at baseline and follow up, and separately by follow-up time point (12 months for recruitment waves 1 to 3, 6 months for recruitment wave 4). Changes from baseline in the proposed outcome measures will be summarised in the same way. All summaries will include the number of observed values and the number of missing values. Continuous variables will be summarised by the mean, standard deviation, median, interquartile range, minimum and maximum. Categorical variables will be summarised as the number and percentage of participants in each group.

The primary and numeric secondary efficacy outcomes will be compared between intervention groups using linear regression analyses predicting change in outcome from intervention group, adjusting for baseline value of the outcome, age and gender.

Binary secondary efficacy outcomes will be compared between intervention groups using logistic regression analyses predicting outcome from intervention group, adjusting for age and gender.

If numbers are too low for the planned regression analysis, unadjusted regression analyses or simple tests will be carried out instead. For numbers below five in any group, no statistical tests will be carried out.

The distribution of the residuals of each linear regression analysis will be reviewed and transformations will be applied to the outcome variable as appropriate.

Regression results will be reported as adjusted mean difference between intervention groups, or adjusted odds ratios for logistic regressions, with 95% confidence interval and p-value.

Missing values will not be imputed.

Health economic analyses will be carried out by health economists and are not part of this SAP.

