### Putative Secondary outcomes

Change from baseline in each continuous secondary outcome measure will be analysed in a linear regression analysis predicting change from baseline from randomised intervention group adjusting for baseline value of the outcome measure, child age and gender.

Binary secondary outcome measures (ECBI problem score > 11 and ECBI intensity score > 127) will be analysed in a logistic regression analysis predicting the outcome from randomised intervention group adjusting for baseline ECBI problem score or ECBI intensity score (as continuous measures), child age and gender.

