### Subgroup Analyses

To assess the impact of the follow-up time on the proposed primary and secondary outcomes, the analysis will be repeated in those participants who have 12-month follow-up only.

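### The pooled linear models mix 6-month outcomes (wave 4) with 12-month outcomes (waves 1-3) and have no term for time point, which costs precision and inflates the pooled residual SD

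*Supplement*

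**What the plan says.** Study Design gives waves 1-3 a 12-month assessment, while "participants of wave 4 will have follow-up assessments after 6 months". Under Randomisation, families are allocated 1:1 and "No stratification or minimisation is applied".

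Section 3.4.1 specifies the PSOC model: "Change from baseline in PSOC will be analysed in a linear regression analysis predicting change from baseline from randomised intervention group", with the baseline score and the child's age and gender as the only covariates. Section 3.4.2 treats the continuous secondary outcomes alike, "adjusting for baseline value of the outcome measure, child age and gender". Table 3.1 runs the PSOC model in the ITT population, which section 2.1 does not restrict by wave. It reports one adjusted difference and one residual standard deviation.

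The SAP recognises the two time points in two places:

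- General Principles promises outcome summaries "separately by follow-up time point (12 months for recruitment waves 1 to 3, 6 months for recruitment wave 4".
- Section 3.4.4 says "the analysis will be repeated in those participants who have 12-month follow-up only", with the stated aim of assessing the impact of follow-up time. Table 3.2 is the PSOC shell for this repeat and has its own residual SD row.

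No model contains wave or time point. The outcome shells come in pooled and 12-month versions only. The one shell confined to wave 4, Table 1.4, concerns retention.

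**The concern.** The length of follow-up is known for every family and is fixed by wave, so it is an obvious candidate covariate. If mean change differs between 6 and 12 months, leaving it out has two effects.

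- The arms may by chance hold different shares of 6-month outcomes. In a given trial this moves the estimate; over repeated randomisations it appears as extra variance.
- The shift between time points is counted as residual noise, so the pooled residual SD is too large for planning a trial with one follow-up time.

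The 12-month repeat does not measure what section 3.4.4 says it is for. It sets a sample against a subset of itself. The two results share most of their families, and any gap between them mixes follow-up time, wave and the smaller sample.

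**Working it through.** **The plan's own figure.** Sample Size and Power: 100 approached × 0.60 response × 2/3 retention = 40 families, 20 per arm. This reproduces. The SAP gives no SD, effect size or power to check.

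**Assumptions, since the documents give no figures.**

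- Wave 4 share p = 0.25 (four equal waves, so 10 of 40 completers).
- Outcome SD 1 and baseline correlation 0.6, so residual SD = √(1 − 0.6²) = 0.8.
- Shift in mean change between 6 and 12 months of 0.2, 0.5 or 1.0 outcome SD.
- No blocking that balances the arms within a wave (the SAP mentions none).

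**Chance imbalance.** The SD of the between-arm difference in 6-month share is √(2 × 0.25 × 0.75 / 20) = 0.137, about 14 points. The 95% range is ±1.96 × 0.137, about ±27 points. At the edge of that range a 0.5 SD shift moves that trial's estimate by 0.27 × 0.5 = 0.13 SD.

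**Residual SD.** With d = shift / 0.8, leaving out the term multiplies the residual SD by √(1 + p(1−p)d²). A sample size proportional to the variance rises by p(1−p)d². Here p(1−p) = 0.1875.

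| Shift (outcome SD) | d | Residual SD ratio | Excess sample size |
| --- | --- | --- | --- |
| 0.2 | 0.25 | 1.006 | 1.2% |
| 0.5 | 0.625 | 1.036 | 7.3% |
| 1.0 | 1.25 | 1.137 | 29.3% |

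For p from 0.15 to 0.35, p(1−p) runs from 0.1275 to 0.2275. The excess at a 0.5 SD shift then runs from 5% to 9%.

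**Simulation of the planned regression.** 40 families, 20 per arm, 10 in wave 4, true effect zero, residual SD 1, 4,000 trials per setting:

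| d | Residual SD, without / with term | Empirical SE, without / with term |
| --- | --- | --- |
| 0.2 | 1.004 / 1.001 | 0.327 / 0.331 |
| 0.5 | 1.023 / 0.999 | 0.340 / 0.336 |
| 0.8 | 1.060 / 0.999 | 0.355 / 0.338 |

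Mean estimates stayed within 0.014 of zero with and without the term. The term costs about 1% in SE when the shift is small and gains about 5% at d = 0.8.

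**The case against.** The strongest case on the other side is that this is a feasibility trial whose three research questions concern willingness, recruitment and retention, and acceptability. The efficacy outcomes are only putative. Pooling everyone and repeating the analysis at 12 months is a defensible choice, and Table 3.2 already gives an estimate and a residual SD for a single time point. All of this stands and limits the weight of the point. The repeat has a price: about 15 per arm under the assumptions above, so an SE larger by √(20/15) = 1.15.

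A reader might infer more than the documents support:

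- **That the intervention estimate is biased.** It is not. Allocation is random, so imbalance in wave share adds variance, and that variance enters the residual SD and the confidence interval.
- **That a full trial would be some 30% too large.** That needs a 1.0 SD shift, which nothing in the documents suggests, and use of the pooled SD for planning, which no section states. At 0.2 SD the excess is about 1%.
- **That the SAP ignores follow-up time.** Sections 3.3 and 3.4.4 and General Principles all address it.
- **That a group-by-time-point interaction is needed.** Time point coincides with wave, so an interaction could not separate follow-up time from cohort or delivery. With five wave 4 families per arm its SE is about 0.8 × √(2/5 + 2/15) = 0.58. With 10 wave 4 families among 40 split 20/20, the chance that one arm has fewer than five is 1 − C(20,5)²/C(40,10) = 72%. If the SAP's bar on tests below five per group covers those cells, the interaction would usually not be run.
- **That the logistic models need the term too.** The ECBI models already carry four predictors, with at most 20 of 40 families in the rarer class. A fifth is hard to justify.

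**Conclusion.** The point holds for the pooled linear models of PSOC and the continuous secondary outcomes. Their estimate and residual SD refer to no single time point, and a known source of variation is left out. The consequence is lost precision and an inflated pooled residual SD: about 0.6%, 4% or 14% for shifts of 0.2, 0.5 or 1.0 outcome SD. These figures rest on the assumed quarter share in wave 4 and residual SD of 0.8. What remains open despite the 12-month repeat is which residual SD would inform a full trial, and where the promised 6-month outcome summaries will appear. The change is worth making because it is cheap. It does not call the trial's feasibility conclusions into question.

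**What to change.** 1. In sections 3.4.1 and 3.4.2, add time point (6 v 12 months, equivalent to wave 4 v waves 1-3) as a covariate in the pooled linear models, subject to the low-numbers fallback in General Principles. Change the model descriptions in the matching shells.
2. State that the residual SD carried to a full trial is the time-adjusted one or the 12-month one in Table 3.2, not the unadjusted pooled one.
3. Add the 6-month outcome tables that General Principles already implies.
4. In section 3.4.4, describe the repeat as giving the 12-month estimate, not as assessing the impact of follow-up time.

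The covariate removes the mean shift from the residual. It does not separate a 6-month effect from a 12-month effect, so the pooled estimate remains an average over the two and should be described as such.

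Cost: one degree of freedom per linear model, a slight loss of precision if the shift is negligible, one extra set of tables, and SAP wording. No new data are needed.
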